#### Randomization and blinding

A random number table will be generated with a computerized random number generator program. The random allocations will be put into opaque envelopes with sequential study numbers by an independent researcher. Two sets of the envelope will be prepared, one set will be for randomization at the site and another set stored in the investigator’s office for emergency unblinding. Each subject will be assigned with a sequential study number and the corresponding IMP will be prepared according to the allocation by a Chinese medicine pharmacist. In the study, the registered CMP investigators, study subjects and outcome assessors will be kept blind of the allocated intervention.

#### Statistical analysis

Basic demographic data (gender, age, *etc.*) will be descriptively summarized. Continuous variables are presented as mean ± standard deviation (SD) and categorical variables are presented as ratios. Intra group comparisons between baseline and each visit will be conducted by using paired *t*-test (or Wilcoxon signed rank test). Linear mixed model will be used to compare the outcomes between groups. All statistical tests will be two-sided, and *p* < 0.05 is considered significant difference. The statistical analysis will be done by an independent statistician and all analysis will be conducted by SPSS. If there is a significant difference in the use of western medicines between the treatment and control groups, it will be considered and processed as a covariance in the statistical analysis.

In this study, the subject will be deemed as “per protocol” if they have taken the maximum dose or if they stop until getting negative RAT results on two successive days and the major symptoms subside (defined as oral temperature ≤37.2°C, the score of cough and fatigue ≤1) with ≥85% intake compliance. The intake compliance is calculated by dividing the no. of packs of drugs ingested by either:a) the number of packs of core formula the subject should take daily (daily dose) x the number of days from the day of starting drug intake to the day the drug is stopped according to the criteria (e.g., if the subject should take 4 packs of core formula a day, starts taking drug on 1 January, stops at 8 January according to criteria, and has taken 30 packs, the compliance will be (30/(4 × 8)) x 100%) = 93.75%, with the subject deemed as “per protocol”; orb) daily dose x 14 for all other cases (e.g., if the subject should take 4 packs of core formula a day, starts taking drug in 1 January and stops at 3 January because of adverse events, and has taken 12 packs, the compliance will be (12/(4 × 14)) x 100%) = 21.43%, with subject deemed as not “per protocol”.

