## Hypothesis

The combined Yinqiao Powder-Maxing Ganshi Decoction is superior to placebo in improving the major symptoms of mild and moderate COVID-19.

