## Methodology

### Study design

This is a randomized, double-blinded, placebo-controlled trial via telemedicine. Eligible subjects will receive a maximum of 14 days’ treatment with Yinqiao Powder-Maxing Ganshi Decoction (with or without specified additions) or placebo, and will be followed up on days 7, 14 and 35 after receiving medication (day 0).

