### Inclusion criteria

1. Age from 18 to 65 years;2. Tested positive for COVID-19 by RATs, Deep Throat Saliva (DTS) or Throat/Nasal swab RT-PCR tests;3. Patient diagnosed with mild to moderate COVID-19 based on the “Coronavirus disease 2019 (COVID-19) Treatment Guidelines” published by National Institutes of Health, United States;4. Duration of symptoms ≤72 h (Start from the presence of the major symptoms of COVID-19: Fever: oral temperature >37.2°C, or cough score ≥2, or fatigue score ≥2);5. At the moment of screening (or within 2 h before screening), body temperature: >37.2°C6. Diagnosed with pattern of wind and heat invading the exterior (風熱犯表證) and/or pattern of intense exuberance of lung heat (肺熱熾盛證) by a registered Chinese medicine practitioner (CMP) (Diagnostic criteria are the corresponding criteria in the “Diagnosis standards for common syndromes in traditional Chinese medicine (《中醫常見證診斷標準》)” published by “Diagnostic Subcommittee of China Association of Traditional Chinese Medicine (中華中醫藥學會中醫診斷學分會)” in 2008, with ≥20 as the threshold for determination);7. Explicit declaration of willingness to participate in the study at the time of video-conference screening after reading the electronic informed consent form (written consent form will have to be signed after inclusion).

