
### Primary outcome

The time between starting medication and body temperature returning to normal (oral temperature 37.2°C and maintain 24 hours).

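### Within-arm tests of change from baseline at p < 0.05 do not bear on superiority to placebo; show those changes descriptively and rest efficacy on the between-arm comparison already planned

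*Protocol article*

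**What the plan says.** The Statistical analysis section plans two kinds of comparison.

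- Within each arm: "Intra group comparisons between baseline and each visit will be conducted by using paired" t-tests, with the Wilcoxon signed rank test as the alternative.
- Between arms, in the next sentence: "Linear mixed model will be used to compare the outcomes between groups".

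One rule then covers both: "All statistical tests will be two-sided", and p "< 0.05 is considered significant difference". The section uses descriptive language only for the demographic data, so the within-arm comparisons are planned as significance tests.

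The Hypothesis section is about a contrast between arms: the formula "is superior to placebo in improving the major symptoms of mild and moderate COVID-19". The Sample size estimation section is also built on a difference between groups. The primary outcome is "The time between starting medication and body temperature returning to normal", maintained for 24 hours.

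Two features of the design determine what baseline means. The inclusion criteria require symptoms for no more than 72 h and a raised temperature: "At the moment of screening (or within 2 h before screening), body temperature: >37.2°C". The visits set against baseline are days 7, 14 and 35.

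**The concern.** A paired test within one arm asks whether that arm changed. It does not ask whether the arm changed more than placebo. Here the baseline is chosen to be abnormal (fever is an entry criterion) and early in an acute illness, while the comparison points lie one, two and five weeks later. Natural recovery and regression to the mean are therefore part of every within-arm comparison of temperature or symptom score, in both arms.

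Each repeated measure would give 2 arms × 3 visits = 6 p-values, none of which contains a treatment contrast. Two patterns can mislead:

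- Both arms are significant, and the result in the treatment arm is read as evidence of benefit.
- The treatment arm falls below 0.05 and the placebo arm does not, and that difference in significance is read as a treatment effect although the arms were never compared.

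**Working it through.** **The plan's own figure.** The document gives no operating characteristics for the within-arm tests, so there is no figure to reproduce on this point. The number per arm is taken as stated: 38 evaluable, and 48 after allowing for dropout (38 / 0.8 = 47.5, rounded up). The usual formula with the stated difference of 0.5 days and SD of 0.7 gives 2 × (1.960 + 0.842)² × (0.7/0.5)² = 30.8, that is 31 per arm and not 38. That discrepancy is on the conservative side and does not affect what follows.

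**Inputs.**

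- n = 38 per arm (Sample size estimation).
- Two-sided 5% for every test (Statistical analysis).
- No treatment effect: both arms share the same natural change.
- Standardised natural change δ = mean change from baseline / SD of that change. The document gives no value, so δ is an assumption and a range is shown.

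**Formula.** The power P of a paired t-test in one arm comes from the noncentral t distribution with n − 1 = 37 degrees of freedom and noncentrality δ√n, where √38 = 6.164. The arms are independent, so:

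- both arms significant: P²
- active significant and placebo not: P(1 − P)

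| δ (assumed) | δ√38 | P, each arm | Both, P² | Active only, P(1 − P) |
|---|---|---|---|---|
| 0.3 | 1.85 | 0.4370 | 0.1910 | 0.2460 |
| 0.5 | 3.08 | 0.8511 | 0.7244 | 0.1267 |
| 0.8 | 4.93 | 0.9977 | 0.9955 | 0.0023 |
| 1.0 | 6.16 | > 0.999 | > 0.999 | < 0.001 |

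With 48 per arm, P is 0.530, 0.924 and 0.9997 at δ = 0.3, 0.5 and 0.8, and the active-only probability is 0.249, 0.070 and 0.0003.

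**Check by simulation.** This used 5,000 trials of two identical arms with 38 per arm.

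- At δ = 0.5, the first arm was significant in 0.8414 of trials and both arms in 0.7184, so the first arm alone was significant in 0.8414 − 0.7184 = 0.123.
- At δ = 0.3, the corresponding figure was 0.4366 − 0.1862 = 0.250.
- Across the settings run, a between-arm t-test on the same changes rejected in 4.8% to 5.1% of trials. That matches its nominal 5%, or 2.5% in the direction favouring active.

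**Illustration for temperature.** All values are assumed: baseline above 37.2°C, day 7 mean 36.8°C with SD 0.3. The mean fall was 0.88°C with SD 0.47, so δ is about 0.88 / 0.47 = 1.9. The within-arm test was significant in every simulated trial.

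**Which measures this reaches.** The primary outcome is a duration with no baseline value, so a paired test cannot be applied to it. The listed secondary outcomes are rates, times to an event, mortality and drug use. The within-arm tests therefore matter for repeated measures that the trial collects: temperature, symptom scores and oxygen saturation. The first two can be expected to show a large natural change. Oxygen saturation need not.

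**The case against.** The strongest reply is that the plan already has the comparison it needs. The sentence straight after the within-arm tests commits to a linear mixed model between groups, and both the hypothesis and the sample size are framed between groups. A reader who sees only the within-arm sentence might infer that superiority to placebo goes untested, and the document does not support that. Nor does any passage say that efficacy will be concluded from the within-arm results. This part of the reply stands, and it limits the point to a risk of misreading.

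A second reply concerns certainty. A reader might infer that the within-arm tests will be significant whatever the treatment does. That is close to true only where natural change is large. It does not follow for oxygen saturation, and at 0.3 SD each arm is significant in fewer than half of trials. The two misleading patterns also belong to different ranges: active-only significance is common when natural change is modest and almost vanishes when it is large. Counting discordance in both directions would double the figures (2 × 0.246 = 49% and 2 × 0.127 = 25%), but only half of that favours active, and the fair comparator for that half is 2.5%. This reply also stands.

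A third reply is that this is a condensed article, and that ranking one analysis above another is commonly left to a statistical analysis plan. That is fair, and the missing ranking is not counted here as a defect. The point rests on what the article does state: named tests within each arm, under the same significance rule as the between-arm analysis.

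None of these replies gives a reason to keep the within-arm p-values. The mixed model makes them unnecessary for efficacy, and it does not make them a test of the hypothesis.

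**Conclusion.** The point holds as a minor weakness in the choice of analysis. The within-arm tests are planned under the common p < 0.05 rule, they cannot test superiority to placebo, and for temperature and symptom scores they will mostly register natural recovery and regression to the mean.

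If natural change is modest (0.3 to 0.5 SD, 38 per arm), two identical arms give significance on active only in about 25% to 13% of trials, against 2.5% in that direction for a between-arm test. At 0.8 SD or more, both arms are significant in over 99% of trials and the tests carry no information about treatment.

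These sizes rest on the assumed natural change, on roughly normal changes, and on 38 evaluable patients per arm. That most patients with mild or moderate disease recover is a reasonable inference from the population, not something the protocol states. The primary analysis and the sample size are unaffected.

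**What to change.** In the Statistical analysis section:

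1. Delete the within-arm paired tests. Show within-arm change descriptively (mean and SD at each visit), without p-values.
2. State that conclusions on efficacy rest only on the between-arm comparison.
3. For any repeated measure analysed with the planned mixed model, report the between-arm difference with its 95% CI, adjusted for the baseline value of that measure and for the two stratification factors, age group (18–49, 50–65) and vaccine doses (3 or more, 2 or fewer).
4. If between-arm differences in symptom score are reported, label them supportive. The Secondary outcomes section uses the scores only to define remission and disappearance and does not list a score difference as an outcome.

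The cost is a few sentences of wording. Symptom scores, temperature and the stratification factors are already collected, and neither the sample size nor trial conduct changes. What is lost is a set of p-values that carry no treatment contrast. The one thing to guard against is that item 4 could turn into an added endpoint, which is why the label is needed.

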### Study outcomes

#### Assessment

1. The time between starting medication and body temperature returning to normal and the recurrence rate of fever after momentary recovery. Each subject will be issued with the same type of oral thermometer for measurement at 9 a.m. (±2 h) and 9 p.m. (±2 h) daily, with at least 12 h between each measurement. Normal oral temperature is defined as equal to or below 37.2°C. Temperature recovery time is defined as the total number of days between medication starting date and the date of “normal oral temperature for 24 h without antipyretic” (both days inclusive). Subjects are required to measure the temperature until day 14 or on the day when the temperature has remained normal for 24 h, whichever is later.2. The negative rate of RATs at day 14 and negative conversion time. Each subject will be issued with the same type of RAT kits which can be used for at least 14 days for testing at 9 a.m. (±2 h) each day, with at least 24 h between each test. Negative conversion time is defined as the total number of days between the medication starting date and the date of securing two successive negative RAT results (both days inclusive). Subjects were required to undergo testing until day 14 or the day when two successive negative RAT results at least 24 h apart are obtained, whichever is later.3. The remission rate at day 14 and remission time of major symptoms.4. The disappearance rates at day 14 and disappearance time of symptoms. Subjects are required to record the status of their symptoms including major clinical symptoms daily at 9 p.m. (±2 h). Except for fever which is marked as ‘No’ or ‘Yes’ according to whether the oral temperature exceeds 37.2°C, other symptoms will be graded on a scale of 0–4 from “None”, “Mild”, “Moderate”, “Severe” and “Very Severe” depending on the actual feelings of the subject (“None” means the symptom is not present, “Mild” means the symptom is present but does not interfere with daily activities; “Moderate” means the symptom is present and slightly interferes with daily activities; “Severe” means the symptom is present and most daily activities cannot be done; “Very Severe” means the symptom is present and interferes with all daily activities). Major clinical symptoms include fever, cough and fatigue. Remission is defined as oral temperature ≤37.2°C, cough and fatigue score ≤1; disappearance is defined as the symptom being present at day 0 (score >0) but the symptom score is 0 at the date of recording.5. All-cause mortality at the 21st day after stopping the medication.6. Incidence of the progression to severe or critical illness during the trial. The all-cause mortality at the 21st day after stopping the medication and the incidence of the progression to severe or critical illness during the trial will be confirmed by communication with the subjects and/or other related person(s) or checking their medical record in the Hospital Authority. The definitions of severe and critical illness are based on the related definitions of “Coronavirus disease 2019 (COVID-19) Treatment Guidelines” published by National Institutes of Health (severe illness: oxygen saturation in the indoor environment of sea level <94%, oxygenation index [PaO2/FiO2] < 300 mmHg, respiratory frequency >30 breaths/min, lung infiltrates >50%; critical illness: respiratory failure, septic shock, and/or multiorgan dysfunction or failure).7. Utilization rates of antipyretic, Paxlovid and molnupiravir within 14 days and the total dosage(s) of the drug(s) used. In this study, subjects are allowed to take western medicines prescribed for the treatment of COVID-19 under the current guidelines of the Hong Kong Hospital Authority with at least 2 h’ gap between Chinese and western medicines. If oral temperature >39.0°C and continues over 4 h; or the oral temperature >39.5°C, the patient is advised to take antipyretic (paracetamol is recommended as a priority) for acute treatment. Patients need to record the amount and time of the drug(s) used.8. Oxygen saturation. For safety reasons, each subject will be issued with the same type of pulse oximeter for measurement at 9 a.m. (±2 h) and 9 p.m. (±2 h) daily, or whenever the subject decides it is necessary. If the reading is less than 94%, the patient is considered to have severe illness and has reached the end point of the study and is recommended to seek medical attention immediately. Subjects are required to measure their oxygen saturation at rest until day 14 or the time of body temperature returning to normal (continuing for 24 h) or the negative conversion time (2 successive negative RAT results), whichever is later.

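### The stated analysis names no baseline covariate for time to temperature normalisation, although every subject has a qualifying temperature before randomisation; prespecifying it is a cheap, optional gain in precision

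*Protocol article*

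**What the plan says.** The Statistical analysis section covers all between-group comparisons in one sentence: "Linear mixed model will be used to compare the outcomes between groups". It lists no fixed effects. It contains one covariate rule: if western-medicine use differs significantly between arms, "it will be considered and processed as a covariance in the statistical analysis". No baseline variable is mentioned as a model term.

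The primary outcome is "The time between starting medication and body temperature returning to normal", with normal defined as 37.2°C or below, held for 24 hours. Item 5 of the inclusion criteria requires of everyone: "At the moment of screening (or within 2 h before screening), body temperature: >37.2°C". There is no upper limit, and the Assessment section gives antipyretic advice for readings above 39.0°C and 39.5°C, so a range of starting values is expected. Randomisation is stratified by age and number of vaccinations, not by temperature.

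Remission of major symptoms needs a normal temperature together with cough and fatigue scores of 1 or less. At entry those scores appear only in item 4, where symptom onset is dated from "Fever: oral temperature >37.2°C, or cough score ≥2, or fatigue score ≥2".

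**The concern.** A subject who enters at 37.3°C and one who enters at 39.5°C both qualify, but they start at different distances from the endpoint. If starting temperature predicts recovery time, leaving it out of the comparison puts explainable variation into the residual, and the target difference is only half a day. The design does not balance this variable either. Followed as written, the plan could adjust for something that happens after randomisation, and only when a test says so, while leaving unused a value obtained before randomisation on every subject.

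Time to symptom remission raises a similar question. Because item 4 joins its three conditions by alternatives, some subjects may enter with cough and fatigue already at 1 or less and need only lose their fever. Others must improve on all three.

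What is at stake is precision and prespecification. The validity of the test is not in question.

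**Working it through.** **Inputs from Sample size estimation:** SD 0.7 days, difference 0.5 days, two-sided 5% level, stated power 80%, 38 evaluable per arm, 48 per arm after a 20% allowance for dropout.

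**Assumed input:** the correlation ρ between baseline temperature and recovery time. The documents give none, so a range of 0.1 to 0.5 is shown.

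**The plan's own figure.** The normal approximation gives n = 2 × [0.7 × (1.960 + 0.842) / 0.5]² = 30.8, or 31 per arm. The t-test gives 31.8, or 32. Neither is the stated 38. The second step does reproduce: 38 / (1 − 0.20) = 47.5, or 48 per arm and 96 in total. On its own inputs, then, the plan is conservative: a two-sample t-test with 38 per arm has 86.7% power, and with 48 per arm 93.4%.

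**Effect of adjustment.** For an uncensored continuous outcome, residual SD = SD × √(1 − ρ²). For example, at ρ = 0.4 it is 0.7 × √0.84 = 0.642. Putting the residual SD into the t-test power at 38 per arm, and ignoring the one degree of freedom spent out of 74:

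| ρ | Variance removed (ρ²) | Power, SD 0.7 | Gain (points) | Power, SD 0.77 |
|---|---|---|---|---|
| 0 | 0% | 86.7% | – | 79.8% |
| 0.1 | 1% | 87.0% | 0.3 | 80.2% |
| 0.2 | 4% | 88.0% | 1.3 | 81.4% |
| 0.3 | 9% | 89.6% | 2.9 | 83.4% |
| 0.4 | 16% | 91.8% | 5.1 | 86.2% |
| 0.5 | 25% | 94.4% | 7.7 | 89.7% |

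The last column is a sensitivity case. An SD of about 0.77 is what would make 38 per arm give roughly the stated 80%; the plan does not state that SD. There the gain is 0.4 to 9.9 points over the same range of ρ.

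**Chance imbalance.** The part of the unadjusted estimate that is due to baseline imbalance has standard deviation ρ × 0.7 × √(2/38) = ρ × 0.161. That is 0.064 days at ρ = 0.4 and 0.080 days at ρ = 0.5, or 13% and 16% of the 0.5-day target. An imbalance of 1.96 standard errors would shift the estimate by about 0.13 and 0.16 days.

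**Are the covariates available before randomisation?**
- *Temperature:* yes, for every subject, by inclusion item 5. But that item says body temperature, with no site or device. The standard thermometer is described for the daily study readings: "Each subject will be issued with the same type of oral thermometer for measurement at 9 a.m" and again in the evening.
- *Cough and fatigue:* not shown. Item 4 lets fever alone date the onset, so no criterion requires a score from every subject, and Table 1 lists no symptom scoring at screening. Scores are recorded daily from day 0 at 9 p.m. (±2 h), while the medication is split between morning and evening. The day 0 score may therefore follow the first dose.

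**The case against.** The strongest objection is that the point rests on silence. A reader might infer that the model is unadjusted, and the article never says so. It is a condensed account, and a list of model terms commonly sits in a full protocol or analysis plan that is not shown. That stands, so no error has been demonstrated. It does not dispose of the point entirely, because the section does state a covariate rule, and that rule covers only a variable that arises after randomisation.

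A reader might also infer a substantial loss of power. The documents do not support that. The correlation is unknown. Entry restricted to temperatures above 37.2°C and an unstandardised reading, with no stated antipyretic-free condition, could both weaken it. Power on the plan's own inputs already exceeds 80%.

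Nor does chance imbalance mean bias. Randomisation and the unadjusted standard error already allow for it, and the type I error is not inflated.

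Finally, recovery time is a whole-day count observed over about 14 days and may be censored, so the variance formula is only a guide for the primary outcome and does not carry over to the binary remission rate. A baseline term would not settle whether a linear mixed model suits a time outcome. Both observations are correct. They limit the size claimed, but not the case for naming the covariate in advance.

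**Conclusion.** The point holds as an optional improvement. The stated covariate rule names no baseline variable, and a qualifying temperature that measures the starting distance to the primary endpoint is available on every subject before randomisation. Prespecifying it would be expected to help, or at worst to cost almost nothing.

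The table's gains, from a fraction of a point of power to nearly 8 at SD 0.7, rest on the assumed correlation and on treating recovery time as an uncensored mean difference. The sample size is unaffected, and the unadjusted comparison would remain valid. A reader might extend the point to baseline cough and fatigue as values already in hand for everyone; the article does not show that they are recorded before randomisation, or before the first dose.

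**What to change.** Add to the Statistical analysis section that the primary comparison includes the pre-randomisation screening temperature as a continuous covariate, in whichever model is used for the time outcome, and regardless of any observed imbalance. Say how that reading is taken (site and device).

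For time to major-symptom remission, include the same temperature. Add baseline cough and fatigue scores only if they are recorded before the first dose; if they are to be used, the study schedule should show that timing. If a separate analysis plan already lists these terms, bring the article's wording into line with it.

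For the primary outcome the cost is a sentence of wording and one degree of freedom, with no new data. The remission-time model would spend up to three degrees of freedom, and a pre-dose scoring time may need to be added.

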### Sample size and statistical methods

#### Sample size estimation

The primary outcome of the study is the time between starting medication and body temperature returning to normal, i.e., the time to fever resolution after the first treatment. Based on previous studies, we assumed the standard deviation (SD) is 0.7, and the time to fever resolution of half a day (0.5 days) would have clinical significance (Qiu et al., 2020; Chen et al., 2021). Therefore, to detect such a difference between groups, 38 in each group will be needed with a power of 80% and a 5% 2-tail significance level. To allow for possible dropouts during the study period, we inflate this value by 20%, hence a total of 96 patients will be needed for the proposed study and 48 in each group (12 in each sub-group).

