#### Subject withdrawal

Subjects can withdraw at any time without having to give any reason. However, our research staff will endeavor to identify the reason(s) and these subjects will be encouraged to attend the follow-up at day 35 or an unscheduled follow-up for assessment to the benefit of subjects.

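### One linear mixed model is named for every between-group comparison, although the primary outcome is a single time to event per subject and the secondary outcomes include unresolved times and yes/no rates

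*Protocol article*

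**What the plan says.** The Statistical analysis section of the protocol article states: "Linear mixed model will be used to compare the outcomes between groups". No outcome is excepted. The only other tests named are within-group ones, the paired t-test or Wilcoxon signed rank test.

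The primary outcome is "The time between starting medication and body temperature returning to normal", with normal temperature held for 24 hours. The Assessment section counts it in whole days with both end dates included, so each subject contributes one number.

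The Secondary outcomes section adds further times (RAT conversion, remission of major symptoms, disappearance of individual symptoms). It also lists single yes/no results: day-14 rates, oxygen saturation below 94%, progression, death and use of other drugs.

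Three provisions bear on incomplete times:
- Subject withdrawal: "Subjects can withdraw at any time without having to give any reason".
- Assessment, at an oxygen saturation below 94%: "the patient is considered to have severe illness and has reached the end point of the study".
- Sample size estimation: "To allow for possible dropouts during the study period, we inflate this value by 20" per cent.

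In the other direction, the Assessment section has subjects "measure the temperature until day 14 or on the day when the temperature has remained normal for 24 h, whichever is later".

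**The concern.** A linear mixed model is built for repeated measurements. With one time per subject and no clustering named, nothing is left for its random part to describe, and it becomes a linear regression of recovery time on treatment. That regression needs a number for everyone. It cannot represent a subject known only to be still febrile when last seen. Such a subject must either be dropped or be given a made-up value, and the article does not say which.

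Subjects who leave because they deteriorate are not a random subset. If they are dropped, the arm with more of them looks faster than it was. If their last day is entered as a recovery day, early exits look like quick recoveries.

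For the yes/no outcomes a linear model does estimate a risk difference. Its intervals assume the same variance in both arms and approximate normality, which is unreliable when events are few, as with death or progression in this low-risk population.

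**Working it through.** **1. The plan's own figure.** Inputs from Sample size estimation: difference 0.5 day, SD 0.7, 80% power, 5% two-sided. n per group = 2 × (1.96 + 0.842)² × 0.7² / 0.5² = 30.8, so 31 (32 with the exact t-test). The stated 38 is not reproduced, which is a separate matter. The next step is: 38 / (1 − 0.20) = 47.5, so 48 per group. The basis is a comparison of two means, which a linear analysis matches. Under these inputs 48 per group gives about 93% power.

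**2. How many fevers would outlast observation?** Under normality with SD 0.7, even a mean of 7 days puts day 14 at (14 − 7) / 0.7 = 10 SD above the mean, so the probability is essentially zero. Measurement also continues past day 14 if needed. Incomplete primary times would therefore come mainly from withdrawal, or from the oxygen-saturation end point if temperature readings stop there.

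**3. What the method does with early leavers.** Simulation, 48 per arm, 1,500 runs per scenario. Assumed: control mean 3 days, times rounded up to whole days, departures unrelated to recovery and spread evenly over 0.1 to 3.7 days. Percentages are control/active. Some of those who leave have already recovered, so about 14% to 16% of times are unresolved in rows 2 to 4, and about 11% in row 5.

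| Scenario | Linear, completers only | Linear, last day entered as recovery | Log-rank |
|---|---|---|---|
| 1. Full follow-up, 0.5-day effect: power | 0.90 | 0.90 | 0.88 |
| 2. 20%/20% leave, no effect: type I error | 0.049 | 0.051 | 0.042 |
| 3. 20%/20% leave, 0.5-day effect: power | 0.85 | 0.65 | 0.85 |
| 4. 10%/30% leave, no effect: type I error | 0.051 | 0.235 | 0.068 |
| 5. As row 4, skewed times (gamma, SD 2): type I error | 0.069 | 0.101 | 0.059 |

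In row 3, entering the last day as recovery shrinks the estimated difference to 0.44 day. In row 4 it creates a false difference of 0.24 day in favour of the arm with more leavers. The simulation error on a 5% rate is √(0.05 × 0.95 / 1500) = 0.006. Departure because of deterioration was not simulated, so these figures do not measure that bias.

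**4. Secondary times.** A day-14 rate below 100% means that some subjects have no event by day 14. RAT testing is meant to run on until conversion, as temperature measurement does until recovery. Disappearance of symptoms is assessed within 14 days, so those times are cut off by design.

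**5. Rare yes/no outcomes.** Suppose, as an illustration, no deaths in either arm of 48. All values are zero, the residual variance is zero, and the linear model returns an interval of zero width. The exact two-sided 95% upper limit for 0 of 48 is 1 − 0.025^(1/48) = 7.4% per arm.

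**The case against.** The strongest defence concerns the primary outcome. Temperature is followed until day 14 or recovery, whichever is later. The planned contrast is a difference in means, and a linear comparison estimates it directly. With full follow-up, or with departures unrelated to recovery and only completers analysed, the linear and log-rank results nearly coincide. The serious error in row 4 needs both unequal departure and a coding that the article nowhere states. All of this stands.

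A reader might go further than the documents allow in three ways:
- **That the main result would be wrong.** The documents do not support this, for the reasons just given.
- **That up to 20% of subjects would lack a recovery time.** The 20% is a planning allowance for the whole study, which runs to day 35. A subject who drops out after the fever has resolved still has a complete primary value.
- **That slow recoverers are lost.** A subject still febrile on day 6 is still being measured and enters the analysis with an observed time.

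A log-rank test is also no cure for informative departure. Censoring at the last reading assumes that leaving is unrelated to recovery, and in row 4 its own type I error is slightly above 5%.

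It could also be said that a fuller plan may settle the methods. But the sentence is a positive statement covering all outcomes, so it would need correcting in any case.

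**Conclusion.** The point holds in a limited form. The plan states one method for outcomes of three kinds, and it suits only the repeated scores. For the primary outcome the consequence is conditional. It is negligible if nearly all fevers resolve under observation. It becomes material if subjects leave before recovery, especially unequally between arms or because they deteriorate, or if their last day is entered as a recovery time. The simulated range runs from no practical difference to a loss of power from 0.85 to 0.65, or a type I error near 0.24. Those figures rest on the assumed control mean of 3 days and the assumed timing and amount of departure.

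For the secondary outcomes the mismatch is more direct: disappearance times are cut off at day 14 by design, and linear-model intervals for rare events are unreliable. The wording should be corrected before unblinding.

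**What to change.** Replace the single sentence with methods by type of outcome.

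- **Primary and other time outcomes:** all randomised subjects, Kaplan-Meier curves and a log-rank test, plus the difference in restricted mean time to day 14 with a 95% CI, which keeps the 0.5-day scale. Medication starts on day 0 and both end dates count, so a recovery on day 14 has a recorded time of 14 − 0 + 1 = 15. State the truncation point on that count.
- **Incomplete times:** censor withdrawals at the last reading, and add a sensitivity analysis because this assumes non-informative dropout. For analysis, count subjects who reach an oxygen saturation below 94% or die before recovery as not recovered through day 14. This leaves the clinical handling of such subjects unchanged.
- **Rates:** logistic regression, risk differences or, for rare events, exact methods.
- **Repeated daily scores:** keep the linear mixed model.

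The cost is a rewritten paragraph and a short sensitivity analysis, with no new data.
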